### Study setting

The study will be conducted on medical oncology departments of both academic and non-academic hospitals in the Netherlands.

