### Sample size

The trial is powered to detect an independent effect of the two interventions on observed SDM, as assessed with the OPTION12 [62, 63], a widely used instrument to assess SDM in consultations. There is no agreement on what constitutes a clinically meaningful difference on the OPTION12. The sizes of the effects of SDM interventions on OPTION12, including decision aids and physician training across different specialties and in both simulated and clinical settings, range from 0.5 to 1.5 [41, 64, 65]. As most reported large effect sizes, we adopted an effect size of d = 0.8 in the sample size calculation. We expected that the effect of the combination of the oncologist training and the patient communication aid will be larger, but not twice as large (estimated effect size = 1.2). To account for this hypothesized antagonistic interaction [66], we decided to adopt a parallel group design instead of a factorial design. Hence, we will examine the effect of the oncologist training among patients allocated to the control condition (between-oncologist comparison) and the effect of the patient communication aid among untrained oncologists (within-oncologist comparison).

SDM will vary by oncologist. ICC’s for the OPTION12 reported in literature [67, 68] and personal communication ([name], Leiden University, the Netherland, May 2014; [name], University Medical Center Hamburg, Germany, July 2014) range from 0.11 to 0.60. In a sample of 47 audio-recorded consultations meeting the same eligibility criteria as the current trial [20], an ICC of 0.19 for OPTION12 scores was demonstrated (unpublished). Since the ICC was 0.20 or lower in the majority of these data sets, a value of 0.20 was adopted in the sample size calculation.

Sample size calculation was based on the effect of the oncologist training (between-oncologist comparison; two-sided t-test taking into account clustered data). The above mentioned criteria, along with a power of >80% and α of 0.05, resulted in a required sample size of 24 oncologists and 192 patients (12 oncologists per arm and 8 patients per oncologist; power = 0.84).

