### Randomization

#### Oncologists (in training)

Oncologists are randomized to receive training or continue their standard practice. Randomization stratifies for working experience (staff versus oncologist in training). Randomization occurs in blocks of 2. To prevent predictable allocation, oncologists are allocated in sets of at least two ‘of a kind’ (either staff or in training). Randomization occurs per hospital to make sure that in each hospital approximately half of the participating oncologists is trained. Randomization lists are created by an independent methodologist. Randomization is performed by an independent researcher.

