### Statistical methods

#### Primary outcome

To account for the hierarchical nature of the data, i.e. patients nested within oncologists, multilevel regression analysis will be used to test the effect of the single interventions on the observed level of SDM in the audio-recorded consultation. Analysis will be conducted separately for the OPTION12 and the 4SDM. Random intercept and slope models will be examined. The effect of the oncologist training (level of oncologists) will be established among patients who did not receive a communication aid. The effect of the communication aid (level of patients) will be established among patients of untrained oncologists. Effects with two-sided *p*-values < .05 will be considered significant; 95CI’s as well as effect sizes will be provided. As the OPTION12 is currently the most widely used instrument to assess SDM, an intervention will be considered effective if it had a significant effect on OPTION12 scores. Baseline differences across arms on background characteristics (patient age, gender, educational level) as well as patients’ baseline measures will be examined with the appropriate statistical tests (ANOVA, Chi-squared tests). All analyses of effectiveness will be controlled for differences between arms at baseline as well as the two stratification variables (working status oncologist, type of consultation). All analyses will be intention-to-treat, i.e., all eligible consultations will be included in the analysis (irrespective of whether the communication aid was actually received or read; or whether the oncologist received the full training package).

The hypothesized additional effect of the combined intervention will most likely be smaller than the effects of the single interventions (RQ1). That is, combining the two is hypothesized to increase but not to double the effect of the single interventions. The combination of the training and the aid will be considered more effective than either or both single interventions if (1) the effect size of the combination compared to care as usual is statistically significant and (2) is at least 150% of the effect size of either or both single interventions. The study is not powered to statistically test the difference between the combination and the single interventions.

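### Oncologists are randomised within hospital, but the planned training analysis has no hospital term; if hospitals differ in OPTION12, the test of the training is conservative

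*Protocol article*

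**What the plan says.** The Randomization section for oncologists sets three restrictions:

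- "Randomization stratifies for working experience (staff versus oncologist in training");
- "Randomization occurs in blocks of 2";
- "Randomization occurs per hospital to make sure that in each hospital approximately half of the participating oncologists is trained".

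Study setting confirms that there are several sites: "medical oncology departments of both academic and non-academic hospitals in the Netherlands". The number of hospitals is not given.

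Statistical methods, Primary outcome, describes the data structure and model as "i.e. patients nested within oncologists, multilevel regression analysis will be used". All effectiveness analyses are to control for baseline differences between arms "as well as the two stratification variables (working status oncologist, type of consultation"). Under Secondary outcomes, the only further level is time. Hospital appears nowhere as a covariate or as a level.

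On the comparison concerned, Sample size says "we will examine the effect of the oncologist training among patients allocated to the control condition", and describes this as a between-oncologist comparison.

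**The concern.** Apart from the training condition itself, the two variables named are those used in the patient-level minimisation. The oncologist-level randomisation also used hospital, and that restriction has dropped out of the analysis. The protocol already follows the rule that analyses control for stratification variables; its list is incomplete against its own randomisation section. The clause on baseline differences does not fill the gap, because a factor balanced by design will not show up as an imbalance between trained and untrained oncologists.

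When training is balanced within hospital, differences between hospitals largely cancel out of the trained-versus-untrained contrast. A model without hospital still counts those differences as oncologist-level error. The estimate is not biased, but its reported standard error is too large, its confidence interval too wide and its p-value too high on average.

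This bears on the comparison that sets the sample size and rests on only 24 oncologists. An intervention is declared effective on a two-sided p below .05 for OPTION12, so a conservative test acts directly on the conclusion.

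**Working it through.** **Inputs from Sample size:** d = 0.8 ("we adopted an effect size of d = 0.8 in the sample size calculation"), ICC 0.20, two-sided alpha 0.05, 12 oncologists per arm, 8 patients per oncologist, stated power 0.84. The training comparison uses only patients without the aid, so about m = 4 per oncologist.

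**Assumptions, since the protocol gives neither quantity:** the number of hospitals H is 3, 6 or 12. The share f of the 0.20 oncologist-level variance that lies between hospitals is 0 to 50%. Trained and untrained oncologists are equal in number in each hospital.

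**1. Reproduce the stated power.** The variance of an oncologist mean is 0.20 + 0.80/4 = 0.40. SE = sqrt(2 × 0.40/12) = 0.258 SD. The noncentral t distribution with 22 df gives power 0.842, which matches 0.84. All between-oncologist variance, including any hospital part, counts as error here.

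**2. True SE under balance within hospital.** The hospital part cancels: SE = sqrt(2 × (0.40 − 0.20f)/12).

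**3. SE reported by a model without hospital.** With c = 24/(2H) oncologists per hospital and arm, the expected within-arm variance is (0.40 − 0.20f) + 0.20f × (12 − c)/11. Example with f = 0.25, H = 6, c = 2: 0.35 + 0.05 × 10/11 = 0.3955, so SE = sqrt(2 × 0.3955/12) = 0.257, against a true SE of sqrt(2 × 0.35/12) = 0.242. The ratio is 1.06.

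| Hospital share f | True SE | Reported SE (H = 3 to 12) | Excess |
|---|---|---|---|
| 0% | 0.258 | 0.258 | none |
| 10% | 0.252 | 0.256-0.258 | 2-3% |
| 25% | 0.242 | 0.254-0.258 | 5-7% |
| 50% | 0.224 | 0.249-0.258 | 11-15% |

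**4. Type I error and power.** Simulation of oncologist means (40,000 runs per setting) gives a type I error for the model without hospital of about 0.05 at f = 0, 0.036-0.041 at 25% and 0.027-0.035 at 50%. Power at d = 0.8:

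| Hospital share f | 6 hospitals: without / with fixed hospital effects | 12 hospitals: without / with |
|---|---|---|
| 0% | 0.841 / 0.830 | 0.842 / 0.805 |
| 25% | 0.860 / 0.878 | 0.854 / 0.853 |
| 50% | 0.878 / 0.921 | 0.873 / 0.903 |

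The fair comparison is within a row. When hospitals differ, balance already lifts the power of the unadjusted test above 0.84.

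**5. Effect of drop-out on fixed effects.** Recruitment plans 30 oncologists to keep 24. With 30 randomised in pairs and 6 lost at random (6,000 runs), power without / with fixed hospital effects at shares of 0, 25% and 50% is:

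- 6 hospitals: 0.842 / 0.814, 0.844 / 0.848, 0.872 / 0.902;
- 12 hospitals: 0.828 / 0.733, 0.849 / 0.791, 0.866 / 0.852.

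Broken pairs make fixed effects expensive when hospitals are many and small.

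**The case against.** The strongest reply is that the size of the problem rests on quantities the protocol does not give. With no between-hospital variance nothing is inflated, and at a 10% share the excess is 2-3%. Balance is promised only approximately, and drop-out weakens it. Fixed hospital effects can lose power, as step 5 shows. The error is also on the safe side. All of this stands. It makes the conclusion conditional and shapes the remedy, but it does not restore the missing factor.

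One might also say that an article leaves such detail to the analysis plan. That would excuse silence, but here the adjustment variables are listed and counted as two.

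A reader might infer more than the text supports:

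- **That the standard error is certainly too large.** It is so only if hospitals differ in OPTION12.
- **That adjustment would lift power from the stated 0.84 to 0.88 or 0.92.** This compares across different variance assumptions and roughly doubles the gain.
- **That the benefit of balancing is lost altogether.** The estimate keeps its smaller true variance; only the reported precision falls short.
- **That the sample size is wrong or false positives become more likely.** The 0.84 reproduces without any gain from hospital, and type I error falls below 0.05.
- **That the communication-aid result is equally affected.** That comparison is within oncologist, so hospital differences largely drop out of it.

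**Conclusion.** The point holds in conditional form. The protocol randomises oncologists within hospital and then specifies an analysis of the training effect that leaves hospital out. Whenever hospitals differ in OPTION12, that analysis reports too large a standard error, by the amounts tabulated above for 3 to 12 hospitals.

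With 6 hospitals and balance within each, the recoverable power is about 0.02 at a 25% share and about 0.04 at 50%. The shares and the hospital counts are assumptions, and the calculations use oncologist means with equal numbers per hospital. It is a modest loss of efficiency that is cheap to repair, not a threat to validity.

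**What to change.** In Statistical methods, Primary outcome, replace the count of two stratification variables by the full list: working status, type of consultation, and hospital as a factor of the oncologist randomisation. Account for hospital in the between-oncologist (training) analyses in one of two ways, fixed before unblinding:

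- **Random hospital intercept** with a small-sample degrees-of-freedom correction, for example Kenward-Roger. This is preferable when hospitals are many or pairs are broken, because it spends little when the estimated hospital variance is near zero.
- **Fixed hospital effects**, if hospitals are few, with sparse hospitals pooled.

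The communication-aid analysis does not need the change for this reason.

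The cost is wording and some degrees of freedom; no new data are needed beyond each oncologist's hospital. With fixed effects and no hospital variance, the loss of power is about 0.01 at 6 hospitals (0.841 to 0.830) and about 0.04 at 12 (0.842 to 0.805), and more if drop-out breaks the pairs.

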#### Secondary outcomes

The effect of the interventions on the secondary outcomes will be analyzed in multi-level regression analysis with either 2 or 3 levels, i.e., outcome assessment at different time points (level 1; if applicable), nested within patients (level 2) nested within oncologists (level 3). The effect of the training on the observed level of SDM and general communication skills in simulated patient encounters will be assessed by using a repeated measure ANOVA with time (within subjects, effect of time), condition (between subjects, effect of condition) and time x condition (effect of the training) as independent variables. To present patients’ use and evaluation of the communication aid, the appropriate descriptive statistics will be used (medians, percentages).

## Discussion

Systemic treatment for advanced cancer offers uncertain and sometimes little benefit while the burden can be high. Hence, treatment decisions require Shared Decision Making (SDM). The CHOICE trial examines both the separate as well as the combined effect of an oncologist training and a patient communication aid on SDM regarding palliative systemic treatment.

The trial has several strengths. To our knowledge, it is the first study to test both the separate and combined effect of a patient- and a physician-targeted intervention on SDM about cancer treatment in the palliative setting. A strength of the study is that both the training and the communication aid are tailored for use in initial as well as evaluative consultations about palliative systemic treatment. The far majority of studies on SDM focus on single initial treatment planning consultations. Yet, decision making in the palliative setting is characterized by many and changeable options that do not result in closure. [94] CHOICE prepares both patients and oncologists for different moments of decision making. A strength of the small-group training is that it targets oncologists’ knowledge, attitude and skills by combining many different behavior change techniques [95], such as modelling, education, discussion, role play, a booster and a pocketsize reminder card. A strength of the patient combination aid is that it creates choice awareness among patients, it can be used flexibly regardless of the type and number of available options, and it explicitly targets the two-way flow of information within the conversation. A strength of the study is its randomized controlled trial design, with concealed and computer-generated allocation and blind outcome assessment to prevent bias. Several reviews have called for more robust studies with a low risk of bias to examine the effect of communication interventions [30, 96]. Moreover, the study allows for conclusions about the effect on immediate outcomes, i.e., observed communicative behavior in simulated and actual practice, as well as more distal outcomes, such as the decisions made and patients’ quality of life.

The trial has limitations as well. First of all, it has a pragmatic design [97–99] in which the control condition concerns care as usual instead of a placebo control. Patients and oncologists are not blind for their own condition; and it is likely oncologists are not blind for their patient’s condition either. Knowing one received the intervention of interest may raise expectations and change behavior. Furthermore, we did not adopt cluster-randomization at the level of departments, yet instead randomized individual doctors and patients. This has the risk of contamination, i.e., trained oncologists could influence untrained colleagues and the interaction with patients with a communication aid could influence interactions with patients without the aid in later consultations. Lastly, although we developed a training protocol which is transferable, we cannot rule out that the effect of the training depends on the trainer’s experience, skills and personality.

The findings will be submitted for publication in peer-reviewed scientific journals and will be disseminated at national and international conferences. The results will enable evidence-based choices regarding the investment in SDM interventions targeting either oncologists, patients or both in the advanced cancer setting. Moreover, if proven effective, two evidence-based interventions are available to support oncologists and patients in making decisions about treatment for advanced cancer. Ultimately, the implementation of SDM in the care for advanced cancer patients may enhance the quality of medical decision making, and hence the quality of patients’ (end of) life.

## Abbreviations

4SDM: For measuring Shared Decision Making (instrument)
ANOVA: Analysis of variance
CHOICE: Choosing treatment together in cancer at the end of life (study acronym)
CME: Continuing Medical Education
CONSORT: Consolidated Standards of Reporting Trials
CPS: Control Preferences Scale (instrument)
CT/PET-CT: Computed Tomography/ Positron emission tomography–computed tomography
DA: Decision Aid
DCS: Decisional Confict Scale (instrument)
EORTC-QLQ C30: European Organization for Research and Treatment of Cancer Quality of Life Questionnaire core set (instrument)
ICC: Intraclass Correlation
MAC: Mental Adjustment to Cancer scale (instrument)
Mini-MAC: Mini Mental Adjustment to Cancer scale
OPTION12: Observing Patient Involvement tool (instrument)
PSQ: Patient Satisfaction Questionnaire (instrument)
QPL: Question Prompt List
QQQ: Quality Quantity Questionnaire (instrument)
RCT: Randomized Controlled Trial
SDM: Shared Decision Making
SDMQ-9: Shared Decision Making Questionnaire (instrument)
STAI: Spielberger State and Trait Anxiety Inventory
TiOS: Trust in Oncologist Scale
VAS: Visual Analogue Scale
